##### Cost-effectiveness analysis

The cost-effectiveness gain related to the proposed eradication strategies lies in the comparison with having no strategy at all (doing nothing) and the prevention of infections. “Doing nothing” is not included in this trial because it is considered unethical as we clearly expect no eradication at all. The number of infections is expected to be low in this trial and the positive effects of prevention of infection do extend the time horizon of this trial. Therefore, the prospectively gathered data in this trial will be combined with literature into a Markov model in order to estimate the incremental cost-effectiveness (ICER) from a health care perspective over a time horizon of 5 years. The model is needed to estimate the infection rate in a doing-nothing strategy, to relate infections to quality of life losses, and to extrapolate the trial data. During the trial the quality of life of patients will be assessed by the EQ-5D-5 L at baseline and 6 and 12 months and the result (Dutch tariff) will be used to derive a QALY estimate for each patient according to the trapezium rule. The cost analysis consists of two main parts. First, at the patient level, volumes of care related to the HPN care and infections will be measured by means of the iMTA Medical Consumption Questionnaire (iMCQ). In addition, the medication use will be derived from the electronic patient records. Loss of productivity due to illness or recovery will not be included in the analyses because, on estimation, only 5% of the HPN patients perform paid (or unpaid) labor.

The second part of the cost analysis consists of determining the cost prices for each volume of consumption. The standard cost prices from the “Dutch Guidelines for Cost Analyses” and https://www.medicijnkosten.nl/ will be used. In the end, volumes of care will be multiplied by the cost prices for each volume of care to calculate costs. Two incremental cost-utility ratio’s (ICURs), expressed as costs per QALY gained, will be calculated—one for each strategy compared to doing nothing. Model-based cost-effectiveness analyses will be carried out using probabilistic sensitivity analysis, by Monte Carlo simulation, to take all uncertainties surrounding the input parameters into account. The costs will be included across a gamma distribution, the probabilities and utilities with beta distributions, which is according to the guidelines of the ISPOR. The results of the 5000 simulations will be plotted in cost-effectiveness planes and in willingness to pay curves.

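### The planned cost-utility ratios set each strategy against a modelled doing-nothing option and leave out the step between search and destroy and continuous suppression

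*Protocol article*

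**What the plan says.** The Cost-effectiveness analysis section of the protocol article locates the economic gain in the comparison with having no strategy. That option is not a trial arm: it "is not included in this trial because it is considered unethical as we clearly expect no eradication at all". It therefore enters only through a Markov model that combines trial data with literature, "from a health care perspective over a time horizon of 5 years". The section gives the model's purpose: "The model is needed to estimate the infection rate in a doing-nothing strategy".

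The section then fixes the output. "Two incremental cost-utility ratio’s (ICURs), expressed as costs per QALY gained, will be calculated", and the comparator of both is named: "one for each strategy compared to doing nothing". An ICER is also mentioned, without a comparator. Uncertainty is to be handled "using probabilistic sensitivity analysis, by Monte Carlo simulation, to take all uncertainties surrounding the input parameters into account", with beta distributions for probabilities and utilities, gamma distributions for costs, and 5000 simulations shown in cost-effectiveness planes and willingness-to-pay curves.

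Elsewhere, Randomization allocates patients 1:1 to SD or CS, and the Rationale section aims to find the best of the long-term strategies. Budget impact analysis looks at the consequences of implementing one of them.

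**The concern.** A decision maker here has three mutually exclusive options: do nothing, use CS, or use SD. The ratio that bears on the choice is each option against the next best one that is not dominated. The plan fixes two ratios against the lowest rung and none for the step between the two active strategies. That step is the only part of the comparison supported by randomisation.

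Followed as written, the stated ratios cannot show whether the costlier strategy is worth its extra cost over the cheaper one. Both may fall under a payer's threshold while the step lies above it. One strategy could even be dominated by the other and still show an acceptable ratio against doing nothing.

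**Working it through.** The cost-utility section states no numerical result, so there is no figure of the plan's own to reproduce on this point.

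**Inputs**
- From the protocol article: two ratios, each against doing nothing (Cost-effectiveness analysis); expected one-year eradication of 77% for SD and 55% for CS (Sample size and power calculation).
- Assumed, because the documents give none: costs, QALY gains and loss of carriage without treatment. The documents do not say which strategy costs more; SD is taken as costlier for illustration only.

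**1. What two ratios leave open.** Let C and Q be a strategy's extra cost and QALYs over doing nothing. The planned ratios are R_CS = C_CS/Q_CS and R_SD = C_SD/Q_SD. The step is

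R_step = (C_SD − C_CS)/(Q_SD − Q_CS).

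Rearranged, R_SD = [Q_CS·R_CS + (Q_SD − Q_CS)·R_step]/Q_SD. So, if SD gains more QALYs, R_SD is a weighted average of R_CS and the step. If also R_SD exceeds R_CS, the step must exceed both planned ratios.

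**2. Illustration.** Assume CS costs EUR 2,000 for 0.10 QALY and SD costs EUR 5,000 for 0.15 QALY.
- CS against nothing: 2,000/0.10 = 20,000 per QALY.
- SD against nothing: 5,000/0.15 = 33,333 per QALY.
- SD against CS: 3,000/0.05 = 60,000 per QALY.
- Check: (0.10 × 20,000 + 0.05 × 60,000)/0.15 = 33,333.

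At any threshold between 33,333 and 60,000, both planned ratios pass but the step fails. At an assumed threshold of 50,000, net monetary benefit is 50,000 × 0.10 − 2,000 = 3,000 for CS and 50,000 × 0.15 − 5,000 = 2,500 for SD, so CS is preferred.

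The two ratios alone do not determine the step either. With k = Q_SD/Q_CS, R_step = (k·R_SD − R_CS)/(k − 1). For the same 20,000 and 33,333, this is 66,667 at k = 1.4, 60,000 at k = 1.5 and 46,667 at k = 2.

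**3. The same check with the protocol's eradication rates.** Assume 0.1 QALY per eradicated patient and a net cost of 500 for CS. CS against nothing is 500/0.055 = 9,091.

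| Assumed SD net cost | SD vs nothing (÷ 0.077) | SD vs CS (÷ 0.022) |
|---|---|---|
| 1,000 | 12,987 | 500/0.022 = 22,727 |
| 1,500 | 19,481 | 1,000/0.022 = 45,455 |
| 2,500 | 32,468 | 2,000/0.022 = 90,909 |

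**4. Dependence on the doing-nothing assumption.** Let s be the assumed share of untreated carriers who lose carriage. Keep SD at 1,500, CS at 500 and net costs fixed.

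| s | CS vs nothing | SD vs nothing | SD vs CS |
|---|---|---|---|
| 0% | 9,091 | 19,481 | 45,455 |
| 10% | 500/0.045 = 11,111 | 1,500/0.067 = 22,388 | 45,455 |
| 20% | 500/0.035 = 14,286 | 1,500/0.057 = 26,316 | 45,455 |

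In this simplified structure both planned ratios move with s and the SD-versus-CS ratio does not. The unstated contrast is the one that does not rest on the unrandomised comparator.

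**The case against.** Four points can be made for the plan.

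- *The comparison is partly there.* Table 1 lists healthcare costs and EQ-5D-5L as secondary outcomes, and Secondary study parameter(s) compares parameters between the groups. The model yields costs and QALYs for both strategies, so the step could be derived, and the planes or curves might show it. This stands: the economic contrast is not wholly absent. But the text commits to two other ratios, and separate comparisons of cost and utility are not a cost-utility result.
- *Doing nothing is a relevant option.* The Rationale section says some patients currently get no treatment. This stands, and is why those ratios should be kept, though not as the only ones.
- *No decision rule is tied to the ratios.* The stated aim is effectiveness and safety, tested in the primary analysis. A reader might infer that the trial would recommend a strategy that is poor value; the documents state no such rule.
- *A trial-only ratio would clash with the plan.* The section uses a model because few infections are expected and benefits extend beyond follow-up. This stands, so the step should come from the same model.

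A stronger reading is also tempting: that doing nothing is fixed at zero eradication and both strategies are therefore favoured. The documents do not support it. The expectation of no eradication is given as the ethical reason for having no such arm, not as a model input. The infection rate without treatment is to be estimated with the help of literature, and probabilities get beta distributions. A literature rate for untreated carriers could already include natural loss of carriage, and the documents give no figure for such loss.

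**Conclusion.** The concern holds in this form: the only cost-utility ratios the protocol article fixes set each strategy against an unrandomised, modelled option, and none is stated for SD against CS. This is a positive statement of number and comparator, not a detail left to another document.

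The actual size cannot be computed from the documents. The illustrations (60,000 for the step against 20,000 and 33,333; or 22,727 to 90,909 against 9,091 and 12,987 to 32,468) rest on assumed costs and QALYs with SD as the costlier strategy. The second set also takes QALY gain as proportional to one-year eradication. They show that the gap can be large enough to reverse a choice, not that it will be. The dependence on s also holds net costs fixed, which a five-year infection model would not do.

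Whether zero is used as a model input, and so whether the ratios are biased in favour of both strategies, is not established. The point concerns a secondary analysis and should be corrected because that analysis is meant to inform implementation.

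**What to change.** In the Cost-effectiveness analysis section, replace the two ratios as the main result with a full incremental analysis of doing nothing, CS and SD, using the same five-year Markov model and 5000 simulations:

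- rank the three options by expected cost and remove dominated ones;
- report the SD-versus-CS ICUR and the net monetary benefit of each option;
- show acceptability curves over all three options together;
- keep the two ratios against doing nothing as secondary results.

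As a sensitivity analysis, vary loss of carriage under doing nothing (for example 0% to 20%, an assumed range) rather than rely on the expectation of none. State whether the literature infection rate already includes such loss, so that it is not counted twice.

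The cost is a little more analysis, with no new data and no change to the model's structure. The downside is that the ratio for the costlier strategy may look less favourable.

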##### Budget impact analysis

A budget impact analysis (BIA) will be performed according to the ISPOR principles of Good Practice for BIA. This BIA allows prediction of the financial consequences related to the adaption and implementation of one of the eradication strategies, in order to determine the affordability of the intervention. Data will be used that reflect the size and characteristics of the HPN population in the Netherlands together with the results of this trial (effect sizes, resource use, etc). When relevant, budget impact analyses are generated as a series of scenario analyses.

### Quality and safety

In general, this study aims to restrict the physical and mental burdens for the subject as much as possible. The physical risks that are introduced by this study to the participants are believed to be minimal. The risk derived from collecting the culture swabs is negligible if performed by well trained physicians, nurse practitioners, and/or the patient’s own caregiver. For this, we will provide an information brochure and give instructions during the outpatient clinic visit. Next to this, the systemic antibiotics as prescribed in the SD group have the potential risks of causing side effects, certain toxicities and allergies, or intolerance. These potential risks, however, are all well known because the antibiotics that are prescribed are part of the routine care and are prescribed following the current national guidelines. During the study sufficient medical health assistance (nurse practitioners, attending physician or principle investigator) will be present at all times in the hospital and reachable by phone to cope with unexpected events. Serious adverse events will be reported through a web portal to the central committee on research involving human subjects (in Dutch: Centrale Commissie Mensgebonden Onderzoek) and the accredited institutional review board (https://www.toetsingonline.nl/). The remaining events are recorded in an electronic database and reviewed annually by an independent monitor.

### Monitoring

During the trial, two independent monitors (one in the Netherlands and one in Denmark) will visit the sites yearly to check the completeness of patient records, the accuracy of entries on the CRFs, the adherence to the protocol and to Good Clinical Practice (GCP), the progress of enrollment, and also to ensure that trial devices are being stored, dispensed, and accounted for according to specifications.

## Discussion

This trial will provide guidance for further policy development and implementation of (long-term) *S. aureus* decolonization protocols and other novel infection/transmission preventive strategies. HPN patients, and likely other chronic patient groups such as hemodialysis patients, will benefit from an evidence-based effective and safe long-term *S. aureus* decolonization protocol. Ultimately such a protocol will lower *S. aureus* infections and reduce subsequent hospitalizations, catheter removals, mortality, antimicrobial resistance, and costs.

We believe that with this project we can gain essential knowledge that fills a significant gap in our current understanding of (long-term) *S. aureus* decolonization treatments. As such, the CARRIER trial will prove the efficacy of a long-term *S. aureus* decolonization strategy in HPN patients for the first time. The study will give insight into other important outcome measures such as antimicrobial resistance, *S. aureus* transmission, patient compliance and—as a completely new feature—the role of the caregiver and his/her carrier status.

During the trial, antibiotic drugs will be used according to the national MRSA eradication guidelines [10]. These drugs are also used in clinical practice for eradication of methicillin-sensitive *S. aureus* (MSSA) since there is no separate guideline for MSSA eradication. The MRSA guideline based their advice on studies that were not restricted to the eradication of MRSA only, but included studies evaluating MSSA eradication as well. There is no evidence that any of the treatment options included in the MRSA guideline have a more favorable risk:benefit ratio in the HPN population. Allowance of different treatment regimens that are included in the MRSA guideline enables us to include patients with certain allergies or potential interacting co-medication as well. This is in line with current clinical practice and enables us to include enough patients to answer the research question.

From the patients’ perspective, the trial will have many advantages as well. Implementation of the trial results might lead to less morbidity (less hospitalizations and complications such as *S. aureus* infections and catheter removals) and eventually a lower mortality. In addition, we think that the results of this study will most likely have an impact on daily clinical practice, since our aim is to implement the findings in the (inter)national guidelines on chronic intestinal failure in adults.

Strengths of this trial include its multicenter, randomized controlled design in different international centers, which will increase the (international) generalizability of the study. Besides this, barely any studies have investigated effective long-term *S. aureus* eradication strategies. The outcomes include mostly objective measures to determine successful *S. aureus* eradication: the results of bacterial cultures and the additional whole-genome sequencing in some cases. The questionnaires used for the subjective patient-reported outcomes (e.g., impact on overall quality of life (QOL), treatment satisfaction, and health care related costs) are well-accepted, reliable, and mostly validated (TSQM vII, EQ-5D-5 L and iMCQ). Lastly, the burden for patients is expected to be minimal since the feasible treatment protocol chosen has limited impact on daily life.

In summary, the findings of this study will help to determine what the most effective and safe long-term *S. aureus* decolonization strategy in HPN patients is. The trial will determine the relative contribution of two different decolonization strategies on successful eradication, reduction of catheter-related bloodstream infections (CRBSIs), and eventually a lower mortality.

## Trial status

Currently, the trial is ongoing and patient recruitment started at the end of 2017. The estimated end date will be in Q4 of 2019.

## Abbreviations

AE: Adverse event
ANOVA: Analysis of variance
BIA: Budget impact analysis
CRBSI: Catheter-related bloodstream infection
CS: Continuous suppression
EQ5D-5 L: EuroQol 5 dimensions, 5 levels
HPN: Home parenteral nutrition
ICUR: Incremental cost-utility ratio
iMCQ: iMTA Medical Consumption Questionnaire
ISPOR: International Society for Pharmacoeconomics and Outcomes Research
MRSA: Methicillin-resistant *Staphylococcus aureus*
MSSA: Methicillin-sensitive *Staphylococcus aureus*
NGS: Next-generation sequencing
QALY: Quality-adjusted life year
QOL: Quality of life
SAB: *S. aureus* bacteremia
SAE: Serious adverse event
SD: Search and destroy
SNP: Single nucleotide polymorphism
SWAB: Stichting Werkgroep AntibioticaBeleid
TSQM: Treatment Satisfaction Questionnaire for Medication
